## Abstract

**Background:**

Faced with a life-threatening illness, such as cancer, many patients develop stress symptoms, i.e. avoidance behaviour, intrusive thoughts and worry. Stress management interventions have proven to be effective; however, they are mostly performed in group settings and it is commonly breast cancer patients who are studied. We hereby present the design of a randomized controlled trial (RCT) evaluating the effectiveness and cost-effectiveness of an individual stress-management intervention with a stepped-care approach in several cancer diagnoses.

**Method:**

Patients (≥ 18 years) with a recent diagnosis of breast cancer, colorectal cancer, lymphoma, prostate cancer or testicle cancer and scheduled for adjuvant/curative oncology treatment, will consecutively be included in the study. In this prospective longitudinal intervention study with a stepped-care approach, patients will be randomized to control, treatment as usual, or an individual stress-management intervention in two steps. The first step is a low-intensity stress-management intervention, given to all patients randomized to intervention. Patients who continue to report stress symptoms after the first step will thereafter be given more intensive treatment at the second step of the programme. In the intervention patients will also be motivated to be physically active. Avoidance and intrusion are the primary outcomes. According to the power analyses, 300 patients are planned to be included in the study and will be followed for two years. Other outcomes are physical activity level, sleep duration and quality recorded objectively, and anxiety, depression, quality of life, fatigue, stress in daily living, and patient satisfaction assessed using valid and standardized psychometric tested questionnaires. Utilization of hospital services will be derived from the computerized patient administration systems used by the hospital. The cost-effectiveness of the intervention will be evaluated through a cost-utility analysis.

**Discussion:**

This RCT will provide empirical evidence of whether an individually administered stress-management programme in two steps can decrease stress as well as maintain or enhance patients’ physical activity level, quality of life and psychological well-being. Further, this RCT, with a stepped-care approach, will provide knowledge regarding the cost-effectiveness of an individually administered stress-management programme whose aim is to help and support individual patients at the right level of care.

**Trial registration:**

ClinicalTrials.gov Identifier: NCT 01588262.

## Background

Faced with a life-threatening illness, such as cancer, many patients develop stress symptoms, i.e. avoidance behaviour, intrusive thoughts and worry [1]. These are all common symptoms of post-traumatic stress disorder (PTSD), which is defined in the Diagnostic and Statistical Manual of Mental Disorders - Fourth edition (DSM-IV) [2] as a phobic and anxious reaction in the wake of a traumatic experience. Life-threatening illnesses were included as a potential traumatic event in 1994, and since then PTSD has been registered as a secondary diagnosis in many cancer patients [2]. Horowitz and colleagues [3] define avoidance as a constrict of ideas, denial of the event (both its meaning and its consequences) and emotional numbing, while intrusion includes unbidden thoughts and images, troubled dreams, repetitive behaviour and waves of feelings. PTSD has been investigated in breast cancer patients [4,5], but little is known about its prevalence among other cancer diagnoses [6,7]. A recent study from Sweden reported that, compared to age-matched controls, men diagnosed with prostate cancer had an increased risk of psychiatric treatment for depression, PTSD and use of antidepressants, regardless of risk group and treatment strategy [8]. In another study, Smith and colleagues [9] concluded that the impact of a cancer diagnosis and treatment persists over the years for many cancer survivors. Therefore, early identification of those at risk could enable treatment to minimize PTSD symptomatology.

Nordin and Glimelius [10] reported that the early identification of those in need of psychological support at a later stage of treatment is possible through screening for clinical levels of worry or depression in combination with intrusive thoughts in individuals with cancer. Further, it has been reported [11] that the effects of cancer treatment on an individual’s quality of life could be predicted using measures of avoidance behaviour. Impaired general health as well as deterioration of both physical and social functioning were correlated with extensive avoidance behaviour at the start of treatment. Since the research has been quite static regarding how to properly select, through screening, the individual patient in order to help and support him/her at the right level of care, there is a need to expand the body of knowledge [12,13].

For patients in states of intense stress, the occurrence of PTSD can be reduced if cognitive behaviour therapy (CBT) is provided one to three months after a traumatic event [14]. Also, methods based on CBT have proven to be able to improve health-related quality of life (HRQoL), reduce psychosocial stress and increase perceived personal control of treatment side-effects and disease symptoms in cancer patients [15,16]. However, at present there is a lack of solid research findings for comparisons of cost-effectiveness and outcome [14].

In the “Breast Cancer and Stress” project (BAS project) [17], the research group wanted to evaluate the effectiveness and cost-effectiveness of a stress-management intervention for breast cancer patients about to start adjuvant therapy. Methods based on CBT were used and the intervention was administered in two steps. In the first step, all participants were offered a low-intensity intervention. Thereafter, patients were screened regarding clinically relevant levels of avoidance, intrusion, anxiety and depression, and those who reported clinically relevant levels were offered more intensive treatment in Step 2 of the programme. Patients who consented to participate in Step 2 were randomized to a more intensive stress-management intervention, either in a group setting or individually. The hypothesis was that half of the individuals assigned to a low-intensity intervention would have significantly improved after treatment. For individuals who continue to have symptoms after low-intensity treatment, it is hypothesized that continued treatment in a group setting with high-intensity interventions will be more cost-effective than individual treatment.

However, since the BAS project was planned and carried through, several reports have been published describing that interventions maintaining or enhancing patients’ physical activity level were successful in decreasing stress and increasing quality of life as well as psychological well-being [18]. Anti-depressant effects have also been reported to be caused by exercise in self-referred cancer patients undergoing chemotherapy [19]. Level of physical activity as well as sleep hours relate to psychological well-being and quality of life in cancer patients [20]. Therefore, we wanted to study whether the stress management offered in the BAS project could be improved using a supplement whereby the counsellors performing the intervention specifically worked with motivating the participants to maintain or increase their physical activity level during and after adjuvant/curative treatment. Further, since there is a lack of knowledge regarding individual stress-management interventions in diagnoses other than breast cancer we decided to include various cancer diagnoses, as well as both men and women. In addition, since studies reporting on the cost-effectiveness of stress-management interventions by means of cost-utility analysis (CUA) are scarce, the interventions in the stepped-care approach will be evaluated using CUA.

This paper presents the design of a randomized controlled trial evaluating the psychosocial effects and cost-effectiveness of an individual stress-management intervention, using a stepped-care approach, for patients with various cancer diagnoses. The intervention is based on CBT, and includes encouragement to be physically active. The hypothesis is that a low-intensity intervention will be sufficient for half of the individuals to maintain or improve their psychological well-being after treatment. For individuals who continue to have symptoms after low-intensity treatment, it is hypothesized that continued treatment with high-intensity interventions will be more cost-effective than that of the control group, which entails treatment as usual.

Specific research questions are:

• Are there any differences between patients who received an intervention based on CBT and those who did not, as regards intrusive thoughts, avoidance behaviour, anxiety, depression, sleep duration and quality, and/or moderate-vigorous-intensity physical activity level?

• Is a stress intervention administered at a low or intensive level a cost-effective way to support patients with cancer?

• Is it possible to predict at baseline which patients are in need of a shorter (low level, Step 1) or longer (intensive level, Step 2) intervention?

## Method

### Patients

Patients (n = 300) over the age of 18 years, with a recent diagnosis of breast cancer, colorectal cancer, lymphoma, prostate cancer or testicle cancer and scheduled for adjuvant and/or curative treatment in the form of chemotherapy, radiation therapy and/or hormonal therapy at the Department of Oncology and Medical Physics, Haukeland University Hospital (Department of Oncology), Bergen, will be consecutively included in the present study. Criteria for exclusion are an ongoing psychiatric condition or language deficiencies in Norwegian.

### Design

The study is a prospective, longitudinal intervention study with a stepped-care approach whereby patients will be randomized to individual stress-management intervention (I) or control (C), treatment as usual. A stepped-care treatment model seeks to treat patients at the lowest appropriate level in the first instance, only 'stepping up' to intensive/specialist services if clinically required. One of the key concepts in the stepped-care model is that treatment methods of varying intensities are matched to the needs of the individual patient [21]. In Step 1, all patients who are randomized to individual stress management will be given a low-intensity treatment (I-a). Those patients who do not improve after this treatment will be given a more intensive treatment (I-b) in Step 2. This makes the intervention more cost-effective, since the intensity of the treatment is adjusted to meet the needs of the individual patient. For a more detailed overview of the design, see Figure 1.

**Figure 1 F1:**
[figure not shown]
The Study design.

### Interventions

In the individual stress-management intervention the sessions will be 45-60 minutes long, and will take place at the Department of Oncology or be conducted by telephone if the patient has been discharged from the hospital. If patients live at a great distance from the hospital some parts of the intervention may be conducted by telephone, which has been shown to have a similar effect [22]. The individual stress-management intervention is planned to be completed within six-months of inclusion.

#### Step 1 (I-a)

All patients will receive one counselling session when they start adjuvant/curative therapy at the Department of Oncology, and a follow-up session face-to-face or over the telephone. At the first session a thorough evaluation of the patient’s psychosocial status will be conducted, according to a model used in a previous study [23]. At the first session patients will receive written information about causes and symptoms of stress, self-care measures to influence stress such as a daily registration of events and behaviour, scheduled behavioural and physical exercises, along with a short relaxation training. Patients who do not report clinically significant levels of stress at the six-week assessment will only participate in these two sessions. They will, however, be evaluated regularly for two years (see Figure 1).

#### Step 2 (I-b)

Patients who report clinically significant levels of stress, such as intrusive thoughts/avoidance behaviour (measured using the Impact of Event Scale (IES) [3]) and/or worry and depression (measured using the Hospital Anxiety and Depression Scale (HADS) [24]) at the six-week assessment will be included in Step 2. Step 2 includes more intensive stress management, with the remaining four to seven sessions devoted to the themes “What is stress?”, “What are the symptoms of stress?” and “Irritability, relationships, the body and pleasure, as well as an orientation towards the future”. These topics are based on an earlier intervention [25]. At all sessions the counsellor will motivate the patient to maintain or increase his or her physical activity level during and after the cancer treatment. At the final session, the counsellor will evaluate the patient’s use of the material and ability to manage his or her stress reactions.

#### Control group (C)

This condition includes the care offered to all patients, e.g. all study participants and non-study participants at the Department of Oncology. It consists of regular contact with the patient’s own doctor and hospital staff, as well as the opportunity to take part in the common rehabilitation programme, including patient education and physical training.

### Recruitment

Patients with a previously listed cancer diagnosis will be invited as soon as a decision has been made to initiate treatment for cancer. Eligible patients will receive written information about the study by post, informing them that they will be contacted by telephone within a week by a member of the project staff. During this telephone call the patients will have the opportunity to ask questions and receive oral information about the study, before they decide whether or not they would like to participate. If they agree to participate they will receive a questionnaire by post containing a request for a written informed consent and baseline questionnaires. A physical activity monitor will be mailed to participants when the baseline questionnaires have been returned (Measure 1). Thereafter patients will be randomized to one of the two conditions, intervention or control. In consultation with each patient who is randomized to the individual stress-management intervention (I), an appointment for the first session will be decided. Individual stress-management treatment will be conducted by specially trained staff at the Department of Oncology, who will schedule appointments after consultation with the patient. Staff members conducting the treatment will receive ongoing supervision throughout the project by a senior researcher.

### Data collection

Data will be collected using valid, psychometrically tested and standardized self-reported questionnaires. Primary outcome (intrusion and avoidance) will be measured using the Impact of Event Scale (IES) [3]. Secondary outcomes regarding psychological well-being will be collected using the Hospital and Depression Scale (HADS) [24], “Daily Stress” (VS-20) [26], Short Form Health Survey (SF-36) [27] and Chalder’s Fatigue Questionnaire (FQ) [28].

Physical activity level as well as sleep duration and -quality will be recorded using the SenseWear™ Pro_3_ Armband (Armband (BodyMedia Inc., Pittsburgh, PA, USA), according to manufacturer instructions, for seven consecutive days [29]. The SenseWear™ Pro_3_ Armband is an activity monitor that is easily applicable, estimates energy expenditure from five (both physiological and mechanical) outputs, and has been found to be valid during free-living activities [30] as well as in groups of cancer patients [31].

The generic Euro Quality of Life 5-Dimensional Classification (EQ-5D) [32] will be used assess health status, and is suitable for health economic analyses. Data from medical records will be used to obtain patients’ demographic and medical background, and information on the utilization of hospital services will be collected from the hospitals’ computer systems/medical records. Information on the utilization of other professional care facilities will be collected from patients’ self-reports. Information regarding sick leave will be collected through self-reports. Attendance at the individual sessions will be recorded by the counsellor.

In addition, the intervention as well as the treatment programmes offered through the regular services of the Department of Oncology will be evaluated using the Client Satisfaction Questionnaire (CSQ-8) [33].

All questionnaires will be sent to the patients’ homes together with a stamped, pre-addressed envelope. Patients who have not returned the completed questionnaires after 14 days will be contacted by telephone by a member of the project staff to ensure as high a response rate as possible.

### End-points and statistical analysis

Power calculations have been done for the IES based on data from another study [23]. On the basis of these conditions (power = 0.8, p = 0.05 and effect size = 0.59), at least 128 patients must be included in each group to detect a significant difference on the IES. To account for the expected dropout and loss of follow-up rates of 15%, we intend to include 300 patients. ANOVA will be used to analyse differences between groups and for repeated measures over time of the continuous variables, while nominal (categorical) variables will be tested using chi square (exact). Although all the criteria for normal distribution are not met with this selection, the parametric tests are sufficiently robust to be used. Patients’ levels of stress-related symptoms will be categorized according to standardized cut-off points. A hierarchical linear regression analysis will be used to examine which variables predict stress symptoms and the utilization of health care services, as well as sick leave and return to work. Net values of the total health care costs will be calculated for the intervention and control groups. Cost–utility analysis (CUA) using quality adjusted life years (QALYs) is a general approach in health economic evaluation [34,35]. QALY is an overall measure of health outcome that weighs a patient’s life expectancy against an estimate of his or her HRQoL score (measured on a 0–1 scale). Cost-effectiveness ratios (CERs) will be calculated as (Δ intervention costs + Δ health care costs)/ Δ QALYs for intervention compared with control. The number of QALYs gained/lost relative to baseline will be calculated for each patient assigned to the intervention or control group as the area under the baseline-adjusted utility curve.

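### The stated power (0.8), significance level (0.05) and effect size (0.59) do not lead to 128 patients per group; on the ordinary two-sample reading they lead to about 47.

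*Protocol article*

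**What the plan says.** The Protocol article gives its sample-size reasoning under End-points and statistical analysis. The calculation concerns the Impact of Event Scale (IES), which carries the primary outcomes, and its basis is external: "Power calculations have been done for the IES based on data from another study". The inputs and the resulting group size are given together: "power = 0.8, p = 0.05 and effect size = 0.59), at least 128 patients must be included in each group".

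The next step adds an allowance for attrition: "To account for the expected dropout and loss of follow-up rates of 15%, we intend to include 300 patients". The Abstract (Method) presents the total as the product of this reasoning: "According to the power analyses, 300 patients are planned to be included in the study". The Patients section repeats 300.

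There are two arms; under Recruitment, "patients will be randomized to one of the two conditions, intervention or control". The article does not name the type of effect size, an SD, the sidedness or the test used for sizing.

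**The concern.** Power, significance level, effect size and group size are tied together: any three fix the fourth. All four are printed here, and they do not agree on the usual reading for a two-arm comparison of a continuous score.

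This sentence is the article's only statement of what the trial can detect on its primary outcomes. A reader who takes it at face value will think that the trial was built to find a difference of 0.59 SD and would be likely to miss much smaller ones. If 0.59 is a standardised difference, the planned numbers can in fact detect about 0.35 SD, which changes how a null result should be read. Conversely, if 0.59 and 80% are what was intended, the inputs call for far fewer patients than 300, and the justification offered for the recruitment target does not support it.

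**Working it through.** **Inputs**
- From End-points and statistical analysis: power 0.80, p = 0.05, effect size 0.59, 128 per group, 15% loss, 300 in total.
- From Recruitment: two arms.
- Assumed, because not stated: a two-sided test, equal allocation, and 0.59 as a standardised mean difference d.

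**Step 1: try to reproduce 128 per group.** The normal approximation is n per group = 2(z₀.₉₇₅ + z₀.₈₀)² / d².
- (1.960 + 0.8416)² = 7.849 and 0.59² = 0.3481.
- n = 2 × 7.849 / 0.3481 = 45.1, rounded up to 46.
- The exact noncentral-t calculation gives 46.08, rounded up to 47.

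The stated 128 is not reproduced: 128 / 47 = 2.7.

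**Step 2: power at the stated size.**
- d × √(n/2) = 0.59 × √64 = 4.72.
- 4.72 − 1.96 = 2.76, which corresponds to power of about 0.997. The noncentral t also gives 0.997.

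**Step 3: difference detectable with 80% power.**
- At 128 per group: 2.8016 × √(2/128) = 0.350; noncentral t, 0.352.
- At 127.5 per group (300 × 0.85 / 2): noncentral t, 0.352.

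**Step 4: does 300 rest on 128 per group?** 2 × 128 = 256, and 256 / 0.85 = 301.2, so 300 follows to within rounding. The words about each group are therefore carried through to the total and are not an isolated slip. From the stated inputs the same step gives 2 × 47 / 0.85 = 110.6, or 111 patients.

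**Step 5: other readings.** Patients needed per group, with 80% power and two-sided 0.05 unless noted:

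| Reading | n per group |
|---|---|
| One-sided 0.05 | 37 |
| Two-sided 0.025 (two primary outcomes) | 56 |
| 90% power | 62 |
| 95% power | 76 |
| Two-sided 0.01, 95% power | 105 |
| Rank test at its worst-case efficiency | about 55 |
| Change scores, zero correlation with baseline | 91 |
| 0.59 as Cohen's f (d = 1.18) | 12 to 13 |
| Effect halved to 0.295 | 182 |

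Reading 128 as a total does not help either, since the total needed is 94. None of these gives 128.

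**Step 6: readings that do give 128, each needing something the article does not state.**
- A raw difference of 0.59 would need an SD of 0.59 / 0.3515 = 1.68.
- If 0.59 is a probability of superiority, Noether's rank-test formula at one-sided 0.05 gives (1.645 + 0.8416)² / (12 × 0.25 × 0.09²) = 6.183 / 0.0243 = 254.4 in total. That is 127.2 per group, rounded up to 128. The two-sided version gives 162 per group.

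**The case against.** The strongest defence is that failure to reproduce depends on what 0.59 is. The article does not say, the calculation rests on a study that is not at hand, and a journal article may leave the effect-size type, SD and sidedness to the full protocol. The rank-test reading in Step 6 does arrive at 128 per group. In addition, if 0.59 is a standardised difference, the trial is larger than the inputs require, and no planned analysis uses 0.59.

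Part of this stands. The missing details are not a finding in themselves, and the calculation cannot show which number is wrong. The rank-test reading, however, is conjecture: it needs a one-sided test and an index that is not named, and the same section commits to parametric methods. The defence does not remove the mismatch among the figures that are printed.

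Some stronger readings are tempting but not supported:
- A reader might infer that the effect size or the power is definitely the wrong entry. The slip could equally be in 128. For instance, 128 is the total (64 per group) for d = 0.50, but nothing in the article shows that a total was mistaken for a group size.
- A reader might infer that the trial is underpowered. For 0.59 as a standardised difference, the opposite holds.
- A reader might infer that 300 should be cut to about 111. That presumes that 0.59 is the right target, which the article does not establish.
- A reader might note that 300 less 15% leaves 255 against 256 needed. That is rounding, not an error in the attrition step.
- A reader might take 0.59 to be the effect observed in the cited study. The article says only that the calculation was based on data from it.

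**Conclusion.** The sample-size statement is wrong as written. On the ordinary two-sample reading, its inputs need about 47 per group against the stated 128. At 128 the power for 0.59 is about 99.7%, not 80%, and 80% power is reached at about 0.35 SD. Because 300 is derived from 128 per group, the printed power and effect size do not describe the planned trial.

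This rests on 0.59 being a standardised mean difference, a two-sided 0.05 test and equal allocation. Changing the sidedness, significance level or power within the usual range does not close the gap. Only an unstated index or SD would. The documents do not settle which of 0.59, 0.8 and 128 is at fault. The consequence is for how the result is interpreted and how the recruitment target is justified, not for a shortage of patients.

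**What to change.** Keep 300 patients. Check 0.59, 0.8 and 128 against the source calculation and restate the sentence so that the figures agree.

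- If 0.59 is a standardised difference, suitable wording is: *With 300 patients randomised and 15% loss, about 127 evaluable patients per group give 80% power at two-sided 0.05 to detect a standardised difference of about 0.35 on the IES, and over 99% power for a standardised difference of 0.59.*
- If 0.59 is a misprint, correct it.
- If 0.59 is a raw difference or another index, name it.

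In the last two cases, give the SD where one is needed, the sidedness and the test used, so that 128 per group can be reproduced.

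The cost is a check of the original calculation and a change of wording. Recruitment and conduct are unaffected.

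### The primary IES comparison is fixed as ANOVA with no adjustment for baseline IES, in a two-year repeated-questionnaire trial that expects 15% loss; a baseline-adjusted mixed model would be more precise at almost no cost

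*Protocol article*

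**What the plan says.** All places are in the protocol article.

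- **Outcome** (Data collection): "Primary outcome (intrusion and avoidance) will be measured using the Impact of Event Scale (IES"). Both scores are treated as continuous.
- **Method** (End-points and statistical analysis): "ANOVA will be used to analyse differences between groups and for repeated measures over time of the continuous variables". The other model in that section, a hierarchical linear regression, is for predicting symptoms, service use and return to work, not for comparing the arms.
- **Baseline** (Recruitment): the activity monitor is posted "when the baseline questionnaires have been returned (Measure 1"), and randomisation follows. Every randomised patient should therefore have a baseline IES. Baseline adjustment is mentioned only for the QALY calculation.
- **Size and loss** (End-points and statistical analysis): with "power = 0.8, p = 0.05 and effect size = 0.59", the plan states that "at least 128 patients must be included in each group". To cover "expected dropout and loss of follow-up rates of 15" per cent, "we intend to include 300 patients".
- **Follow-up** (Abstract; Step 1; Data collection): two years of repeated assessments by posted questionnaire, with a telephone contact if nothing has come back after 14 days. The number of waves is not in the text; the design figure is not shown.

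**The concern.** The article makes a positive choice of method for its primary outcome, and that choice fits the design poorly in two ways.

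First, a baseline measurement of the primary outcome is in hand for everyone, and ANOVA as described makes poor use of it or none. Either baseline is outside the model and contributes nothing, or it is one of the repeated measures. In the second case the group-by-time test subtracts it with full weight instead of the weight that the data support.

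Second, conventional repeated-measures ANOVA needs a complete set of waves per patient. Over two years of posted questionnaires, a patient who misses one form drops out of the analysis although the rest of that patient's data are available.

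At stake is precision on the primary outcome: a wider interval, or a larger smallest detectable effect, for the same 300 patients.

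**Working it through.** **The plan's own figures.** Two-sided 0.05 and 1:1 allocation are assumed, since neither is stated, and 0.59 is read as a standardised mean difference.

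- n per group = 2 × [(1.960 + 0.842)/0.59]² = 45.1, so 46. The stated 128 is not reproduced. It corresponds to an effect of 2.802 × √(2/128) = 0.35 SD. This is a separate matter and is noted only because it affects how the loss of precision reads.
- The dropout step does reproduce: 256/0.85 = 301.2, against 300 planned. Conversely 300 × 0.85 = 255, or 127.5 per group.

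**Cost of not adjusting, one follow-up time.** Let r be the baseline-to-follow-up correlation, with equal variances. The documents give no r; 0.4 to 0.6 is assumed. Relative variances of the group difference are 1 for follow-up only, 2(1 − r) for change from baseline, and 1 − r² for baseline-adjusted.

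| r | follow-up only / adjusted = 1/(1 − r²) | change / adjusted = 2/(1 + r) |
|---|---|---|
| 0.4 | 1.19 | 1.43 |
| 0.5 | 1.33 | 1.33 |
| 0.6 | 1.56 | 1.25 |

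Detectable effect at 127.5 per group, 80% power, r = 0.5:

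- follow-up only or change: 2.802 × √(2/127.5) = 0.351 SD
- baseline-adjusted: 0.351 × √0.75 = 0.304 SD

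**Cost of not adjusting, mean of m follow-up waves.** Assume equal correlation r between all waves and m = 3 to 5. The follow-up mean has variance v = [1 + (m − 1)r]/m, change has v + 1 − 2r, and the adjusted analysis has v − r². For r = 0.5 and m = 4 these are 0.625, 0.625 and 0.375, a ratio of 1.67 for both unadjusted forms. Over r = 0.4 to 0.6 the ratio to the adjusted analysis is 1.43 to 2.00 for change and 1.36 to 2.12 for follow-up only. Adjustment is more precise in every case computed.

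**Complete cases.** The 15% alone leaves 255. If those who stay also miss each of four follow-up waves independently with probability p (assumed), 255 × (1 − p)⁴ remain: 235 at p = 2% and 208 at p = 5%. Widening to 3 to 5 waves and p = 3% to 10% gives about 233 down to 151.

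**Both together.** A simulation used 150 per group, four follow-up waves, a true effect of −0.30 SD and about 68% complete, with dropout depending on arm and earlier score. The complete-case group-by-time contrast had standard errors 0.119, 0.099 and 0.085 at r = 0.4, 0.6 and 0.7. A mixed model with a common baseline mean had 0.073, 0.069 and 0.063. The squared ratios are 2.7, 2.1 and 1.8. The mixed model was given the true covariance, which flatters it slightly.

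**Bias in the same simulation.** The group-by-time contrast averaged −0.285 to −0.292 and the mixed model −0.296 to −0.300. With the same dropout mechanism in both arms the group-by-time contrast averaged −0.296 to −0.299. The difference in bias is at most 5% of the effect.

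**The case against.** The strongest reply is that the article condenses a fuller protocol. The analysis set, missing-data rule, covariates and primary contrast may be settled elsewhere, and their absence here is no finding. That stands, and nothing here rests on those gaps. What remains is that the article does name a method, and a baseline-adjusted mixed model would replace that method rather than fill in its detail.

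A second reply is that the sizes depend on unstated inputs (r, number of waves, intermittent missingness), and that telephone reminders will limit missed forms. This also stands; the figures are ranges under assumptions. Against the stated effect of 0.59, even 208 complete patients give about 99% power. Against the 0.35 SD that 128 per group implies, they give about 71%.

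Some stronger readings are tempting and are not supported:

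- *That ANOVA will give a biased answer.* This needs dropout that depends on observed scores and differs by arm, which the documents do not indicate. Even then the group-by-time contrast was nearly unbiased, and neither method is protected if data are missing not at random.
- *That the analysis averages in pre-treatment visits and so dilutes the effect.* The text shows one pre-treatment wave. The six-week assessment comes after Step 1 has begun and before Step 2. The article does not say that baseline is a level of the time factor or that the group main effect is the primary test.
- *That incomplete patients will be deleted as a rule.* This is the default of the conventional method, not a stated rule.
- *That an as-treated comparison is planned.* The first research question speaks of "differences between patients who received an intervention based on CBT and those who did not", but Design and Recruitment form the groups by randomisation and the QALY calculation goes by assignment. The phrase is loose wording.

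**Conclusion.** The point holds as one of precision. The article fixes ANOVA for the primary IES outcome without baseline adjustment, although a pre-randomisation IES is collected and 15% loss is expected. At one follow-up time, a change-type test has 1.25 to 1.43 times the variance of the adjusted analysis for r = 0.6 to 0.4; at r = 0.5 the detectable effect is about 0.35 SD instead of 0.30 SD. If ANOVA is run in its conventional complete-case form, the plan's own loss rate leaves 255 against a target of 256. One patient is rounding, but there is no margin for intermittently missed waves.

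The direction does not depend on the assumed inputs within the ranges tried; the size does. It rests on r, the number of waves, the intermittent missingness, equal variances and 1:1 allocation. The change should be made, but the plan as written does not invalidate the trial, and a reduction in bias can be offered only as a conditional benefit.

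**What to change.** In End-points and statistical analysis, replace the ANOVA sentence with wording such as:

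> IES intrusion and avoidance will each be analysed by a linear mixed model for repeated measures with group, visit, group-by-visit interaction and baseline score, and an unstructured covariance. Patients will be analysed in the group to which they were randomised. The primary effect is the adjusted group difference at [time point to be named by the sponsor].

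Baseline may enter as a covariate, in which case patients with at least one follow-up contribute. Alternatively it may enter as an outcome with a mean constrained to be common to both groups, in which case all randomised patients contribute. The text should say which. The sponsor must name the primary contrast and follow-up time; the documents do not fix them, and the model does not choose them. The same model should serve the continuous secondary outcomes.

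The cost is a change of analysis wording. Baseline IES is already collected before randomisation, and no patients, visits or questionnaires are added. The change should be made and dated before outcome data are examined by group.
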